#### **6.1.2 Placebo**

Placebo will be manufactured to have a similar formulation and presentation as study vaccine. The production process starts with allantoic fluid of chicken embryos that have not been inoculated with any influenza virus. A lyophilizate also containing the same concentrations of stabilizers as LAIV is then made and filled in ampoules. Microgen has transferred the manufactured placebo back to IEM where it has been securely stored.

#### **6.1.3 Acquisition**

The investigator or study coordinator, if applicable, will be personally responsible for vaccine receipt and management or will designate a person who will be responsible for these activities. PVS and IEM will determine with the investigator or the person in charge, the

date(s) and time(s) of delivery of vaccine to the study site. Study vaccine and placebo, manufactured by Microgen, will be supplied to the study site by IEM.

The person in charge of vaccine receipt will check that the cold chain was maintained during shipment: continuous verification of temperature and/or cold chain monitoring card. In case of any problem, he/she must alert PVS and IEM and Microgen immediately.

The acknowledgments of receipt of study vaccine and placebo will be dated and signed by the person in charge of vaccine at RII. Copies will be kept for archiving at the investigator's site and copies will be returned to PVS (for study vaccine and placebo) and IEM.

#### **6.1.4 Packaging and Labeling**

Study vaccine and placebo will be packed identically, but each package will clearly identify each study vaccine and placebo as such.

#### **6.1.5 Storage and Stability**

LAIV H7N3 and placebo should be stored at a temperature between +2 degrees Celsius (°C) to +8°C (in a refrigerator). Storage temperature should be monitored daily and documented on an appropriate form. Back-up power or storage should be available in case of primary power failure. Study vaccine and placebo should never be frozen. The study vaccine or placebo should not be used if the ampoule is broken, the label is illegible or the physical properties (color and transparency) are altered.

In case of accidental disruption of the cold chain, the products should not be administered and the investigator or the responsible person should contact the Sponsor and PVS to receive further instructions. In such cases, the investigator must receive written consent of the PVS before any study vaccine or placebo may be used.

### **6.2 Dosage, Preparation and Administration of Study Products**

#### **6.2.1 Dosage**

Dosage of study vaccine or placebo will be two doses given 28 days apart. Each dose will be a total of 0.5 ml of prepared study vaccine or placebo, with 0.25 ml delivered intranasally into each nasal passage using a spray dosing device.

#### **6.2.2 Preparation and Administration**

Directly before inoculation of study vaccine or placebo, the contents of an ampoule must be dissolved in 0.5 ml of water for injections for 3 minutes. The dissolved product is a pale yellow, slightly opalescent liquid. The dissolved product should be used within 30 minutes.

For preparation and intranasal administration, a spray dosing device with disposable applicator is used. The spray dosing device consists of a sterile syringe with scales of 40 and 100 units (GOST R ISO 10993, GOST 24861-91, GOST 25026-81), a sterile needle, and one adjustable end cap actuator-183.016 for the creation of a fine spray mist.

To prepare and administer study vaccine or placebo, the complete process is as follows:

- The needle will be placed on the syringe, and 0.5 ml of water for injections will be drawn (to the mark of 20 on the scale of 40 units or to the mark of 50 on the scale of 100 units).
- The ampoule of study vaccine or placebo will be opened, and the 0.5 ml of water added from the syringe.
- After 3 minutes for dissolution of study vaccine or placebo, 0.25 ml of the now-liquid preparation will be drawn into the syringe (to the mark of 10 on the scale of 40 units or the mark of 25 on the scale of 100 units).
- The needle will be removed and placed on a clean or sterile surface, and the spray actuator will be placed tightly on the syringe.
- With the subject seated in a comfortable position with the head slightly tilted back, the tip of the spray actuator will be brought up to the subject's **right** nostril and inserted 0.5 centimeters (cm) into the nasal passage, and the hub of the syringe strongly depressed to inject the product into the nasal passage. After the spray of vaccine into the nostril, the subject should remain in the seated position with the head slightly tilted back for 1 minute.
- After the first spray, the spray actuator will be removed and placed on a clean or sterile surface, and the needle will be replaced on the syringe. Another 0.25 ml of liquid preparation will be drawn into the syringe.
- The needle will once again be removed, and the spray actuator again placed on the syringe.
- With the subject seated in a comfortable position with the head slightly tilted back, the tip of the spray actuator will be brought up to the subject's **left** nostril and inserted 0.5 cm into the nasal passage, and the hub of the syringe strongly depressed to inject the product into the nasal passage. Again, after the spray of vaccine into the nostril, the subject should remain in the seated position with the head slightly tilted back for 1 minute.

## 6.3 Accountability Procedures for Study Products

Study vaccine and placebo must be kept in a secure place. The investigator or the person in charge of study product management will maintain records of delivery of the products to the trial site, the inventory at the site, the dose(s) given to each participant, and the destruction or return of unused doses.

## 6.4 Concomitant and Unauthorized Products

### 6.4.1 Concomitant Medications/Treatment

If an accompanying pathology is other than a criterion for exclusion of a volunteer from participation in the trial, then the relevant treatment should be performed under its usual scheme. All concomitant medicines used should be allowed by the Protocol (see Section 6.4.2 "Unauthorized products"). Information on the concomitant products (trade name, dosage or change in dosing, indications, start date, and termination date) must be reflected

in the appropriate section in the CRF. All subsequent changes in concomitant therapy during the trial must also be reflected in the CRF.

Women included in the trial who are using oral contraceptives for pregnancy prevention should continue taking these products during the entire trial. Use of such products must also be documented in the CRF.

#### **6.4.2 Unauthorized Products**

Any concomitant MIBPs (medical immunobiological products) (including blood preparations), as well as other immune-modulating drugs are contraindicated.

The said products may be prescribed for life-saving purposes.

#### **6.4.3 Use of Unauthorized Products or Products Not Stipulated by the Protocol**

If during the trial a situation arises where there is an adverse reaction or AE requiring treatment and prescription of unauthorized products or products not stipulated by the protocol, then such products may be prescribed. However, PVS and Microgen must be informed within 24 hours. Information on the products (trade name, dosing or change in dosing, indications, start date, and termination date) must be recorded in the CRF. All subsequent changes in treatment during the trial must also be reflected in the CRF. Follow-up of the subject by the investigator will continue until the end of the subject's condition which was the cause for this violation of the protocol (in the case of early withdrawal from the trial) or to the end of the subject's schedule period of participation (to termination).

If any subject is required to take unauthorized products or products not stipulated by the protocol in order to treat an adverse reaction requiring withdrawal, then the investigator should follow procedures for Handling of Withdrawals.

## **7 Study Schedule**

It is the responsibility of the investigator to strictly observe the intervals between visits/procedures. These intervals are precisely defined for each subject in accordance with the protocol and are reflected in the study schedule outlined below. Where not specified, time windows (for example, plus or minus a certain number of days) are not allowed.

### **7.1 Screening**

Prior to inclusion into the vaccine study, subjects will be screened through multiple procedures, including laboratory testing, medical history interview and physical examination. Because screening procedures are required to assess eligibility, they will be performed under a screening ICF (ICF A) prior to the subject providing informed consent for study participation in vaccination and follow-up activities under a second vaccine trial informed consent form (ICF B) (see Section 14).

---

### **7.1.1 First Screening Visit (14 to 4 Days Prior to Trial Enrollment, Day S1)**

After subjects are consented into the screening process (using ICF A), the following activities will occur:

1. The subject will be interviewed to collect baseline demographic data (name, date of birth, gender, race/ethnicity, etc.)
2. A study clinician will interview the subject to collect a detailed medical history. Study staff will review the information to confirm eligibility prior to conduct of further procedures.
3. A study clinician will perform a physical examination. Results will be reviewed by study staff and with the subject to confirm eligibility prior to conduct of further procedures.
4. Blood (serum and whole) specimens will be collected for testing in a comprehensive metabolic panel (CMP) and by complete blood count (CBC) with white blood cell (WBC) differential. Serum specimens will also be collected for testing for chronic viral infections. Specimen collection information must be documented in specimen collection logs.
5. A urine specimen will be collected for urinalysis testing via dipstick. Specimen collection information must be documented in specimen collection logs.
6. Study staff will instruct the subject on when to return for screening results and for official enrollment into the study and admittance to the isolation unit.

### **7.1.2 Second Screening Visit (Day S2) / Trial Enrollment Day (Day 0)**

For subjects continuing with the screening process, the following activities will occur on Day 0:

1. Subjects must present to the study center by 08:00. Study staff will confirm subject identity.
2. Results of the CMP and CBC with differential will be reviewed by a study clinician and with the subject. Results of serologic testing for chronic viral infections will also be reviewed by a study clinician and with the subject. All results will be reviewed to confirm eligibility prior to conduct of further procedures.
3. For women only, a urine specimen will be collected for pregnancy testing.
4. Study staff will inquire about any new medical events since medical histories were recorded and confirm eligibility prior to conduct of further procedures.
5. A study clinician will perform a physical examination. Results will be reviewed by study staff and with the subject to confirm eligibility prior to conduct of further procedures.
6. A study otolaryngologist will perform an ear, nose, and throat (ENT) examination. Results will be reviewed by study staff and with the subject to confirm eligibility prior to conduct of further procedures.

7. If eligibility is confirmed, all information since the beginning of screening must be recorded on the study CRF.

## **7.2 Vaccination and Follow-up Periods**

Only subjects consented and admitted into the isolation unit may undergo subsequent procedures.

### **7.2.1 Day of First Admission into the Isolation Unit (Day 0)**

1. For eligible subjects, a study clinician will review the procedures for the vaccination study and admittance into the isolation unit. A vaccine study ICF (ICF B) should be completed at this time and the subject admitted into the isolation unit. Upon admittance into the isolation unit, a subject may proceed to undergo procedures related to administration of study vaccine or placebo and evaluation of vaccine safety and immunogenicity.
2. At least two hours prior to administration of study vaccine or placebo, a nasal swab specimen should be collected, followed one hour later by collection of a nasal wick specimen. Specimen collection information must be documented on the CRF and in specimen collection logs. Nasal wick specimens will be sent to IEM for mucosal anti-influenza IgA testing.
3. Prior to administration of study vaccine or placebo, a serum specimen will be collected for anti-influenza serologic assays. A whole blood specimen for isolating PBMCs for assessing cellular immune responses will also be collected at this time. Blood specimens will also be collected for testing a CMP and a CBC with differential. Specimen collection information must be documented on the CRF and in specimen collection logs. CMP and CBC with differential test results from specimens collected on Day 0 need not be obtained and reviewed prior to administration of study vaccine or placebo; these results will only served to define baseline status for subjects.
4. The subject will be administered one dose of study vaccine or placebo. Administration of study vaccine or placebo must occur at least one hour after collection of any nasal swab or nasal wick specimens from the subject.
5. The subject will be observed for two hours after administration in case of any immediate reactions. If the subject experiences an immediate adverse reaction, he/she will be treated and the event will be recorded on the CRF.
6. The subject will be observed throughout the day and any AEs that occur will be recorded in the appropriate section(s) of the CRF.
7. At least 6 hours after administration of study vaccine or placebo, a nasal swab specimen will be collected. Specimen collection information must be documented on the CRF and in specimen collection logs.

---

### **7.2.2 First Day after Administration of Dose One (Day 1)**

1. In the morning between 09:00 and 10:00, a nasal swab specimen will be collected. Specimen collection information must be documented on the CRF and in specimen collection logs. Nasal swab specimens will be split for testing at RII and IEM. Nasal swab specimens should be tested at RII by rRTPCR for influenza A positivity within 30 hours of collection (results reported back to one designated investigator by 14:00 the next day). Nasal swab specimens sent to IEM will be used to isolate potentially shed virus in chicken embryos.
2. Once in the morning and once in the afternoon, study staff will interview the subject about any signs and symptoms the subject might be experiencing. Subjects will be encouraged to spontaneously report any concern or symptom they are experiencing. Any AEs that have occurred will be recorded in the appropriate section(s) of the CRF.
3. A study clinician will perform one scheduled physical examination and record the information on the CRF. Results will be reviewed by study staff and with the subject and any AEs that have occurred will be recorded in the appropriate section(s) of the CRF. Any AEs that have occurred will be recorded in the appropriate section(s) of the CRF and may necessitate additional exams throughout the day.

### **7.2.3 Second Day after Administration of Dose One (Day 2)**

Planned procedures on this day are identical to those on Day 1.

### **7.2.4 Third Day after Administration of Dose One (Day 3)**

Planned procedures on this day are identical to those on Day 1.

### **7.2.5 Fourth Day after Administration of Dose One (Day 4)**

Planned procedures on this day are identical to those on Day 1, except that no nasal swab specimen will be sent to IEM for isolation of potentially shed virus in chicken embryos.

### **7.2.6 Fifth Day after Administration of Dose One (Day 5)**

Planned procedures on this day are identical to those on Day 1.

### **7.2.7 Sixth Day after Administration of Dose One (Day 6)**

Planned procedures on this day are identical to those on Day 1, except that no nasal swab specimen will be sent to IEM for isolation of potentially shed virus in chicken embryos.

### **7.2.8 Seventh Day after Administration of Dose One (Day 7)**

1. In the morning between 09:00 and 10:00, a nasal swab specimen will be collected. Specimen collection information must be documented on the CRF and in specimen collection logs. Nasal swab specimens will be split for testing at RII and IEM. Nasal swab specimens should be tested at RII by rRTPCR for influenza A positivity on this

---

day with results reported back to one designated investigator by 16:00. Nasal swab specimens sent to IEM will be used to isolate potentially shed virus in chicken embryos.

2. Once in the morning and once in the afternoon, study staff will interview the subject about any signs and symptoms the subject might be experiencing. Subjects will be encouraged to spontaneously report any concern or symptom they are experiencing. Any AEs that have occurred will be recorded in the appropriate section(s) of the CRF.
3. A study clinician will perform one scheduled physical examination and record the information on the CRF. Results will be reviewed by study staff and with the subject and any AEs that have occurred will be recorded in the appropriate section(s) of the CRF. Any AEs that have occurred will be recorded in the appropriate section(s) of the CRF and may necessitate additional exams throughout the day.
4. A study otolaryngologist will perform an ENT examination. Results will be reviewed by study staff and with the subject and any AEs that have occurred will be recorded in the appropriate section(s) of the CRF.
5. Blood specimens will be collected for testing a CMP and a CBC with differential. Specimen collection information must be documented on the CRF and in specimen collection logs. Any out-of-normal-range result will be recorded as an AE and discussed with the investigator to determine continued eligibility for dose two of study vaccine or placebo.
6. A urine specimen will be collected for urinalysis testing via dipstick. Specimen collection information must be documented on the CRF and in specimen collection logs. Any out-of-normal-range result will be recorded as an AE and discussed with the investigator to determine continued eligibility for dose two of study vaccine or placebo.
7. Subjects will be given a diary card in which they will be asked to record any local and/or systemic reactions that might appear from Days 7 (after discharge from the isolation unit) to Day 28 (Day 28 being the scheduled day of readmission to the isolation unit for dose two of study vaccine or placebo) and to record any concomitant medications. Subjects will be instructed how to use the diary card on this day. All relevant explanations should be included in the diary card. The diary card will also have contact information for the investigators, should the subject have any questions.
8. The subject will be instructed that if the subject later experiences an AE requiring medical care, the subject should inform the investigator as soon as possible and seek medical care as appropriate. If the subject visits a health care provider, the subject should be sure to inform the health care providers of participation in this study and provide the provider with contact information for the investigator.
9. If the subject's Day 6 and Day 7 nasal swab specimens are influenza A negative by rRT-PCR, the subject will be discharged from the isolation unit and informed of the scheduled date of return to the unit.

---

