  - Acute or chronic clinically significant pulmonary, cardiovascular, hepatic, metabolic, neurologic, psychiatric or renal functional abnormality, as determined by medical history, physical examination or clinical laboratory screening tests, which in the opinion of the investigator, might interfere with the study objectives. Subjects with physical examination findings or clinical laboratory screening results which would be graded 2 or higher on the AE severity grading scale (see Attachments) will be excluded from entry into the study and will be excluded from receipt of dose two of study vaccine or placebo.
  - History of leukemia or any other blood or solid organ cancer.
  - History of thrombocytopenic purpura or known bleeding disorder.
  - History of seizures.
  - Known or suspected immunosuppressive or immunodeficient condition of any kind, including HIV infection.
  - Known chronic HBV or HCV infection.
  - Known tuberculosis infection or evidence of previous tuberculosis exposure.
  - History of chronic alcohol abuse and/or illegal drug use.
  - Claustrophobia or sociophobia.
  - Pregnancy or lactation. (A negative pregnancy test will be required before administration of study vaccine or placebo for all women of childbearing potential.)
  - Any condition that, in the opinion of the investigator, would increase the health risk to the subject if he/she participates in the study or would interfere with the evaluation of the study objectives.
-

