### 9.2.2 Adverse Events

An AE is defined as any untoward medical occurrence in a patient or clinical investigation participant administered a pharmaceutical product, which does not necessarily have a causal relationship with this treatment. An AE can therefore be any unfavorable and unintended sign (including an abnormal laboratory finding), symptom, or disease temporally associated with the use of a medicinal product, whether or not considered related to the medicinal product. The occurrence of an AE might come to the attention of study personnel during study visits and interviews of a study participant presenting for medical care.

Information to be collected on AEs includes event description, time of onset, clinician's assessment of severity, relationship to study product (assessed only by those with the training and authority to make a diagnosis), and time of resolution/stabilization of the event. During hospitalization, in case of fever  $>38.0^{\circ}\text{C}$  the body temperature should be measured every 2 hours until resolution (i.e.  $\leq 38.0^{\circ}\text{C}$ ).

Any medical condition, including any Grade 1 physical examination finding or clinical laboratory test result, that was present at the time that the subject was enrolled should not be reported as an AE. However, if this condition deteriorates (becomes Grade 2 or higher) during the study, it should be recorded as an AE.

AEs should always be graded for severity and relationship to vaccine.

**Severity of Event:** All AEs, including clinical laboratory test results, will be assessed by a study clinician to quantify severity using a protocol-defined grading system. For this protocol, the US Food and Drug Administration "Toxicity Grading Scale for Healthy Adult and Adolescent Volunteers Enrolled in Preventive Vaccine Clinical Trials" will be used (see Attachments), except for fever (see below). For events not included in this grading system, the following guidelines will be used to quantify intensity:

0=None: lack of sign or symptom; normal

1=Mild: events require minimal or no treatment and do not interfere with the subject's daily activities.

2=Moderate: events result in a low level of inconvenience or concern to the subject with therapeutic measures. Moderate events might cause some interference with functioning.

3=Severe: events interrupt the subject's functioning and might require systemic drug therapy or other treatment. Severe events are usually incapacitating.

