#### **9.2.4 Procedures to be Followed in the Event that of Abnormal Laboratory Test Values**

To the extent possible, all normal ranges for clinical laboratory test results will be pre-specified. All abnormal laboratory test values must be documented as an AE, unless that value was Grade 1 at study entry (Day 0) and has not increased in severity grade. Abnormal test values may be considered an SAE if the value rises to the level of severe (Grade 4). Any value not normalizing by the end of the study (Day 56) should be followed by the investigator, as would be done under normal clinical care circumstances. After termination of the trial, the investigator should assure that the subject is referred for medical follow-up, as appropriate.

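### Section 7 records every out-of-range laboratory result as an AE, Section 9 exempts unchanged baseline Grade 1 values, and primary safety category 3 depends on which is followed

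*Protocol*

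**What the plan says.** **Visit steps.** Section 7.2.8 (Day 7) says of blood and urine results: "Any out-of-normal-range result will be recorded as an AE". Sections 7.2.10 (Day 28), 7.2.17 (Day 35) and 7.2.19 (Day 56) carry the same recording rule, and none refers to baseline. On Days 7 and 28 the same sentence sends the result to a discussion of eligibility for dose two.

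**AE definitions.** Section 9.2.4 makes every abnormal laboratory value an AE "unless that value was Grade 1 at study entry (Day 0) and has not increased in severity grade". Section 9.2.2 says that "Any medical condition, including any Grade 1 physical examination finding or clinical laboratory test result, that was present at the time" of enrolment is not to be reported as an AE, but "if this condition deteriorates (becomes Grade 2 or higher) during the study, it should be recorded as an AE".

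**Baseline.** Section 5.2 excludes "Subjects with physical examination findings or clinical laboratory screening results which would be graded 2 or higher on the AE severity grading scale". Section 7.2.1 says Day 0 metabolic panel and blood count results "need not be obtained and reviewed prior to administration of study vaccine or placebo" and serve only to define baseline. Sections 8.2.1.3 and 8.2.1.4 list Day 0 among the collection days and require results before dosing on that day.

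**Use.** Sections 3.2.1, 9.1 and 11.3.1 define four primary safety proportions. The third, all other AEs in the 7 days after any dose, includes abnormal laboratory findings from Days 7 and 35. Section 11.3.1 reports the percentage with each event and with at least one event, with exact 95% intervals, and counts by severity and relatedness.

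**The concern.** Whether a laboratory result is an AE is decided when it is recorded, and the protocol gives staff two incompatible instructions for the same result. The difference reaches a primary outcome. Category 3 is meant to describe what happens after vaccination, yet under Section 7 a subject enters it with a mild abnormality already present, and no worse, before the first dose.

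Section 9.2.4 does not close the gap fully, because its exemption stops at Grade 1. A separate matter is the number of analytes: when any out-of-range value counts, healthy subjects enter category 3 without any vaccine effect, and a real excess in other events becomes hard to see in the at-least-one-event figure. The Safety Monitoring Committee's review of the first 12 subjects also covers AEs and laboratory evaluations.

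**Working it through.** **1. The rules side by side**

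| Laboratory value | Section 7 visit steps | 9.2.4 | 9.2.2 |
|---|---|---|---|
| Grade 1 on Day 0, unchanged | AE | not an AE | not an AE |
| Grade 2 or higher on Day 0, unchanged | AE | AE, read literally | arguably not an AE |
| Normal on Day 0, out of range later | AE | AE | AE |

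The first row is a direct contradiction. The second shows the gap in 9.2.4. In 9.2.2 the words on Grade 1 follow a general reference to any medical condition, so they can be read as an example and not a limit; on that reading 9.2.2 and 9.2.4 differ from each other. The third row is common to all the rules.

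**2. Can a Day 0 value of Grade 2 or higher occur?** Section 5.2 removes such results at the first screening visit, 4 to 14 days earlier, so it should be uncommon. Under 7.2.1 it remains possible, because dosing may precede the Day 0 result. Sections 8.2.1.3 and 8.2.1.4 say the opposite about timing. The protocol gives no frequency.

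**3. How many healthy subjects enter category 3 through laboratory values alone?** The protocol states no expected rate, so there is no figure to reproduce.

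Inputs:
- Analytes: 14 in the metabolic panel (8.2.1.3), 15 in the blood count (8.2.1.4) and 7 on the dipstick (8.2.1.5), so k = 14 + 15 + 7 = 36.
- Visits: Days 7 and 35, so 2 × 36 = 72 results per subject.
- Chance q that a healthy value falls outside its range: not stated, since Section 8.2.1 leaves ranges to be specified before enrolment. Assumed 1% to 5%; 5% corresponds to a 95% reference range.

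Under Section 7, with independent results, P(at least one) = 1 − (1 − q)^(number of results):

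| q | One visit (36) | Days 7 and 35 (72) |
|---|---|---|
| 5% | 1 − 0.95^36 = 84.2% | 1 − 0.95^72 = 97.5% |
| 2.5% | 1 − 0.975^36 = 59.8% | 1 − 0.975^72 = 83.8% |
| 1% | 1 − 0.99^36 = 30.4% | 1 − 0.99^72 = 51.5% |

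Independence overstates this. A Gaussian simulation (20,000 subjects per setting) allowed correlation between a subject's visits up to 0.8 and between analytes up to 0.5. With both at their maximum, the two-visit figure is 71.7% at q = 5% and 25.7% at q = 1%. The range is therefore about 72% to 97% at 5% and 26% to 52% at 1%.

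**4. How much does a baseline exemption alone remove?** Suppose any analyte already abnormal on Day 0 is exempt, which is wider than 9.2.4. With independent results, the chance that an analyte is normal on Day 0 and abnormal on Day 7 or 35 is (1 − q)(1 − (1 − q)²). At q = 5% this is 0.95 × 0.0975 = 0.0926, and 1 − (1 − 0.0926)^36 = 97.0%.

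| Two visits, 36 analytes | q = 5% | q = 1% |
|---|---|---|
| Independent | 97.5% → 97.0% | 51.5% → 51.1% |
| Within-subject correlation 0.8 | 94.5% → 82.9% | 44.8% → 34.1% |
| As above, analytes correlated 0.5 | 71.7% → 60.1% | 25.7% → 21.4% |

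The exemption removes persistent abnormalities but leaves most of the chance component.

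**5. What a high background hides.** Suppose vaccine independently causes some other category 3 event in 30% of subjects. At a 97% background the proportion moves from 97.0% to 1 − 0.03 × 0.70 = 97.9%. At a 5% background it moves from 5% to 1 − 0.95 × 0.70 = 33.5%.

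**The case against.** Section 8.1.1 says AEs are defined in Section 9, and 9.2.4 is the dedicated procedure for abnormal laboratory values. Section 7 could be read as a schedule that yields to it. That is the best defence, but the visit steps are explicit recording instructions, repeated at four visits with no cross-reference, and a general pointer does not cancel them.

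Other points stand and limit the concern:

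- A reader might infer that the primary safety analysis as a whole is swamped. There are four proportions; immediate and solicited reactions are untouched. Only the at-least-one-event figure of category 3 is clearly affected, and the summaries by event, severity and relatedness limit the loss. Placebo subjects are recorded under the same rule, although 10 of them cannot restore contrast to a saturated proportion.
- A reader might infer that the contradiction, or the Grade 2 gap, causes the high background. It does not: most of it comes from counting every new out-of-range value, which 9.2.4 also does.
- A reader might say that neither rule looks at change. Section 9.2.4 does compare with Day 0, for Grade 1 values.
- A reader might expect sites to diverge. The trial has one site; the risk is inconsistency between staff, visits or data queries.
- Values out of range but too mild for Grade 1 cannot be assessed, because the attached grading scale is not shown.

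Broad recording is also a deliberate choice: 9.2.2 says to record an event when in doubt. How far ungraded values should count as AEs is therefore partly a matter of policy. Detailed laboratory tables may properly be left to the Data Analysis Plan, but the conflicting recording instruction is in the protocol itself.

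**Conclusion.** The contradiction is certain from the text: an unchanged baseline Grade 1 value is an AE under Sections 7.2.8, 7.2.10, 7.2.17 and 7.2.19 and not under 9.2.2 and 9.2.4. The literal counting of an unchanged Day 0 value of Grade 2 or higher under 9.2.4 is also real, but it should be uncommon, and 9.2.2 can be read otherwise. Through Days 7 and 35 both reach primary category 3, which can then include abnormalities that predate vaccination.

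The chance component is a separate point whose size rests on an assumption: about 72% to 97% of healthy subjects at 5% out of range, and 26% to 52% at 1%, across the correlations examined. A claim that category 3 will sit at its ceiling is not supported, because the protocol gives no range coverage. Even the lowest case, however, places about a quarter of healthy subjects in the category.

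**What to change.** - Use one recording rule in 7.2.8, 7.2.10, 7.2.17, 7.2.19, 9.2.2 and 9.2.4: a post-dose laboratory result counts as an AE only if it is worse in grade than the same subject's Day 0 pre-dose value, whatever the Day 0 grade.
- Report the category 3 proportion with and without laboratory findings, and show laboratory results by grade and as shifts from Day 0 to each visit. This addresses the chance component, which a baseline exemption alone would largely leave in place.
- Leave the dose-two eligibility discussion of out-of-range results on Days 7 and 28 unchanged, worded so that it does not depend on AE status.
- Reconcile 7.2.1 with 8.2.1.3 and 8.2.1.4 on whether Day 0 results are needed before dosing.

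The cost is wording in the protocol and the CRF completion guidelines. Fewer minor laboratory values will appear as AEs, but all of them stay in the listings.
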